**Figure 1 figure1:**
[figure not shown]
Study flowchart. CAU: care as usual; CliMACT+CAU: Climate - Mind and Act+Care as Usual; EMA: ecological momentary assessment; incl: including.

### Participants

#### Recruitment

Participants will include young people aged 14-25 years with climate change–related distress, who will be recruited from the general population via social media, youth counseling and social services, youth centers, food banks, schools, universities, youth organizations, and climate change– and sustainability-related organizations, groups, and institutions in Mannheim and the Rhine-Neckar region. While recruitment efforts are focused on this region, participants from outside this region can be included. All potential participants will be contacted by the research team, receive full information about this study, participate in a prescreening phone call, and, if they pass the initial screen, complete a full screening for eligibility. Participant appointments can take place on-site or via a certified and encrypted videoconferencing system.

#### Inclusion Criteria

Inclusion criteria are (1) aged 14-25 years, (2) having a score of ≥3.5 on the distress subscale and ≥2.3 on the impairment subscale on the Climate Change Distress and Impairment Scale (CC-DIS) [3]. CC-DIS cutoffs for inclusion represent the average scale mean of the 4 samples used in the validation study by Hepp et al [3]. The age range of 14-25 years is based on what has been widely used in the international youth mental health reform, recognizing that most mental health problems have their onset before the age of 25 years [40], as well as youth developmental considerations regarding the appropriateness of the training.

#### Exclusion Criteria

Young people are excluded from participation if they (1) report current treatment for or a current diagnosis of a severe mental disorder which they received from a professional (*ICD-10* [*International Statistical Classification of Diseases, Tenth Revision*] codes: F32.2, F32.3, F20, F22-29, F30.x, F60.3) or (2) report a significant reduction in functioning in the past 30 days (World Health Organization Disability Assessment Schedule 2.0 ≥41) [41]. The World Health Organization Disability Assessment Schedule 2.0 cutoff for exclusion is based on population norms, representing the 90th percentile on the 36-item version [41]. Other exclusion criteria comprise (3) indications of acute risk to self or others, (4) the inability to provide informed consent, and, in case of minors, no consent by parents or legal guardians, and (5) insufficient German language abilities, per assessment of the investigator.

### Intervention

#### Control Condition: CAU

Participants in the control condition will receive CAU, broadly defined, which includes access to all standard health care and social services. CAU broadly defined will include all public mental health services delivered according to local and national service guidelines and protocols by general practitioners, psychiatrists, clinical psychologists, school psychologists, social workers, psychological counselors, and other public mental health practitioners for mental health promotion, prevention, and treatment [42], available to participants in their living environment.

#### Experimental Condition: CliMACT+CAU

##### Overview

Participants allocated to the experimental condition receive the CliMACT training in addition to CAU. CliMACT will be delivered over a 6-week training period. It consists of an app-based, adaptive EMI and 3 sessions with a trained mental health professional, with a duration of 45-60 minutes, administered on-site or online using a certified and encrypted videoconferencing system. The EMI is geared toward real-time and real-world transfer of training content, principles, and techniques from face-to-face sessions to individuals’ daily lives using an app- and web-based system (InteractionDesigner platform, movisens GmbH). The CliMACT training is based on principles of CFI as well as ACT. Multimedia Appendix 2 provides an overview of the key training components during the 6-week training period. The EMI consists of 3 different delivery schemes of EMI components and EMA-based monitoring.

##### Enhancing EMI Delivery Scheme

During the training phase, participants are successively introduced to new EMI components based on CFI and ACT according to a set schema (see Multimedia Appendix 2; for example, after session 1, participants learn how to conduct specific breathing exercises). Participants can receive reminders for enhancing EMI components at self-set times.

##### Consolidating EMI Delivery Scheme

Participants are asked to practice EMI components that have already been introduced via the enhancing EMI delivery scheme on the following days. When all new tasks have been introduced (week 4), participants are encouraged to practice tasks randomly presented. Consolidating EMI components can be completed in response to reminders at self-set times or on demand.

##### Adaptive EMI Delivery Scheme

Participants’ responses to short, daily EMA questionnaires on momentary affect provide the basis for delivering CFI-based intervention via the adaptive EMI delivery scheme tailored to person, moment, and context. These are offered in moments of high negative affect, that is, when ratings exceed the threshold of an individual’s moving average on any negative affect item by ≥0.5 SDs. A prerequisite for the use of the moving average is that respondents have responded to at least 7 EMA prompts within the past 7 days. If this is not the case, a value of ≥4 on any negative affect item serves as a threshold for the adaptive EMI delivery scheme.

##### EMA-Based Monitoring and Feedback

CliMACT allows young people and mental health professionals to monitor young people’s well-being by delivering visual feedback in terms of reported climate change–related events, activities, affect, and completed training components, via the app and a web-based dashboard function.

The app further uses gamification elements to encourage practice and visualize progress throughout the 6 weeks. It provides FAQs (frequently asked questions) on training-relevant matters and web links to local and national climate change and sustainability-related topics and organizations to demonstrate network opportunities for collective action. The finalized CliMACT training manual, developed as part of the ADVANCE (Addressing Mental Health Vulnerabilities From Adolescence to Older Age: Innovating Prevention Science for Times of Change) project, will be published.

#### Adaptation

Theoretical and evidence-based considerations for interventions for young people with climate change–related distress informed adaptation from the original EMIcompass intervention to the CliMACT training (see Background section). Additionally, suggested adapted materials were reviewed with lived experience experts. Following recommendations from the World Health Organization’s Psychological Interventions Implementation Manual [43], cognitive interviews with 9 individuals with lived experience of subjective climate change–related distress were conducted to assess the understandability, acceptability, and relevance of the study materials (eg, visual design and written content). Feedback indicated good acceptability and primarily led to minor adjustments in wording, which were subsequently incorporated into the materials.

### Measures

#### Feasibility of Trial Methodology

The feasibility of trial methodology will be assessed based on the following criteria: feasibility of recruitment is assessed based on achieving the minimum monthly recruitment rate of 11 in (at least) the month with the highest recruitment rate of the feasibility RCT recruitment period. Feasibility of randomization is assessed based on achieving the minimum monthly rate of 10 participants successfully randomized after successful inclusion in at least 1 month. Retention is assessed using the percentage of retained participants at posttraining and 4-week follow-up.

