### Justification of Sample Size

#### Feasibility RCT

The sample size for this feasibility RCT is primarily determined to address the primary objective to provide the basis for successful recruitment in a fully powered efficacy-effectiveness RCT. Initial sample size planning points to ≈180 participants required for the full RCT. To this end, we set a feasibility limit of a minimum monthly recruitment rate of 11 participants in (at least) the month with the highest recruitment rate of the feasibility trial recruitment period. This lower bound reflects the minimum monthly recruitment rate required to recruit an expected ≈180 participants for a subsequent fully powered RCT within a designated period of 17 months. This study’s population for the feasibility RCT will comprise a maximum of 50 youth aged 14-25 years (n=25 in the experimental and control conditions, respectively) with climate change–related distress. This upper limit of 50 is based on recommendations by Whitehead et al [84] for determining sample size for feasibility RCTs and would reflect a monthly recruitment rate of 17 if recruitment can be completed within 3 months. Thus, the feasibility trial will inform us about the feasibility of the aspired recruitment rate and the possibility of overrecruitment.

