**Feasibility of trial methodology**							
	Recruitment	Monthly recruitment rate of n=11 to n=17 participants in (at least) the month with the highest recruitment rate during the feasibility RCT^b^ recruitment period		Monthly recruitment rate of n=5 to n=10 participants in (at least) the month with the highest recruitment rate during the feasibility RCT recruitment period; recruitment area should be opened to places outside Mannheim and Rhine-Neckar		A monthly recruitment of n<5 participants for all months of the feasibility RCT recruitment period	
	Randomization	Successful randomization of n=10 to n=17 participants in (at least) the month with the highest randomization rate during the feasibility RCT recruitment period		Successful randomization of n=4 to n=9 participants in (at least) the month with the highest randomization rate of the feasibility RCT recruitment period		Successful randomization of <4 participants in all months of the feasibility RCT recruitment period	
	Retention	Retention rate of at least 85% of all randomized participants, for outcome assessment of at least one of the assessment time points at posttraining and 4-week follow-up		Retention rate of at least 75% for outcome assessment of at least one of the assessment time points at posttraining and 4-week follow-up		<75% retention at both posttraining and 4-week follow-up	

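### The recruitment threshold of 11 per month is a 17-month average, but the traffic light tests it against the single best month, so green is probable at rates too slow to reach about 180 within 17 months

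*Protocol article*

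**What the plan says.** Justification of Sample Size (Feasibility RCT) states the planning target: "Initial sample size planning points to ≈180 participants required for the full RCT". It explains the figure of 11 as the "minimum monthly recruitment rate required to recruit an expected ≈180 participants for a subsequent fully powered RCT within a designated period of 17 months". The same section, Measures (Feasibility of Trial Methodology) and Table 1 all apply that figure to one month only; in Measures the criterion is "achieving the minimum monthly recruitment rate of 11 in (at least) the month with the highest recruitment rate of the feasibility RCT recruitment period".

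In Table 1, green is 11 to 17 in the best month, yellow is 5 to 10 in the best month, and red is fewer than 5 in every month. Statistical Analysis (Feasibility) defines green as full feasibility and names recruitment feasibility as the primary objective. No mean rate, total over time or time to complete enrolment enters the light.

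The randomisation light has the same form. Green is "Successful randomization of n=10 to n=17 participants in (at least) the month with the highest randomization rate".

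The length of the feasibility recruitment period is not fixed. Three months appears only as a condition, to explain the upper figure of 17.

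**The concern.** A rate that must hold on average for 17 months is tested against the maximum of several monthly counts. The maximum lies above the mean whenever counts vary, and the gap grows with the number of months. Because enrolment is capped at 50, slower recruitment means more months and so more chances for one of them to reach 11. The light therefore does not carry the meaning that the sample size section gives it.

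This light decides the declared primary objective and underlies the sample size. A green result reached through one good month would be read as support for a 17-month recruitment plan that the average rate does not support. It would also bypass the change of recruitment area that Table 1 ties to yellow.

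The randomisation light shares the weakness. As a best-month count, it does not show what share of included participants is randomised.

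**Working it through.** **Inputs.** Target of about 180 and period of 17 months (Justification of Sample Size); cut-off of 11 in the best month (Measures, Table 1); cap of 50 (Justification of Sample Size).

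**The plan's own figure.** 180/17 = 10.59, rounded up to 11. It reproduces, and it is an average.

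**Example without a model.** Months of 11, 5, 5, 5 and 5 total 31. The mean is 31/5 = 6.2 per month, and 6.2 × 17 = 105 participants. The best month is 11, so the light is green.

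**Probability of green.** Assume independent Poisson monthly counts with constant mean λ over k months. Then P(green) = 1 − F(10; λ)^k, where F is the Poisson distribution function. The count over 17 months is Poisson with mean 17λ, so P(180 reached) = 1 − F(179; 17λ). Months needed for 180 are 180/λ.

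| True rate λ | Expected in 17 months | Months to 180 | P(180 within 17 months) | P(green), k = 3 | k = 5 | k = 6 |
|---|---|---|---|---|---|---|
| 7 | 119 | 25.7 | <0.1% | 27% | 41% | 46% |
| 8 | 136 | 22.5 | <0.1% | 46% | 64% | 71% |
| 9 | 153 | 20.0 | 2% | 65% | 83% | 88% |
| 10 | 170 | 18.0 | 23% | 80% | 93% | 96% |

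For λ = 8, F(10; 8) = 0.816, so k = 5 gives 1 − 0.816^5 = 0.64. The expected best month at λ = 8 is 10.4 over 3 months, 11.4 over 5 and 11.7 over 6. Green becomes more likely than not at a true rate of about 8.2 over 3 months, 7.4 over 5 and 7.1 over 6.

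**Why 5 and 6 months are shown.** Results gives first enrolment in December 2024 and the end of data collection on 25 August 2025, about 8.8 months if counted from 1 December. Subtracting the roughly 3.5 months per participant in Study Design leaves about 5.3 months of enrolment. Subtracting only the 10 weeks of training and follow-up (2.3 months) leaves about 6.5. This is an inference; the article reports no monthly counts.

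**Sensitivity.** If recruitment runs until the 50th participant, P(green) is 71% at λ = 8 and 86% at λ = 9. With overdispersed counts (negative binomial, size 5) it is 88% and 93%.

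**A mean-rate rule for comparison.** A mean of at least 10.59 with 50 participants requires all 50 within 50/10.59 = 4.7 months. The probability of that is 3% at λ = 8, 14% at 9, 36% at 10, 63% at 11 and 83% at 12.

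**Precision of the mean.** The exact Poisson 95% limits for n recruited in T months are χ²(0.025; 2n)/(2T) and χ²(0.975; 2n+2)/(2T). For 50 in 5 months they are 7.4 and 13.2 per month.

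**The case against.** The best-month rule is openly stated and identical in all three places, so the text does not contradict itself. It can be read as a test of attainable capacity. The light is also not the only safeguard: the Discussion provides for adapting sites and strategies and for consulting the advisory group before the definitive trial. Over three months, green is less likely than not at 7 or 8 per month. The cut-offs were set in advance and data collection has ended, so replacing the primary light now would be post hoc.

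Most of this stands and limits the point. The capacity reading does not rescue the rule, because the sample size section justifies 11 by a 17-month total and makes no argument from peak capacity. Widening recruitment later is the action tied to yellow, so a misleading green removes its trigger.

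A reader might infer more than the documents support:
- **That yellow changes nothing.** Its action is "recruitment area should be opened to places outside Mannheim and Rhine-Neckar", while the Recruitment section already says "participants from outside this region can be included". Admitting people from elsewhere is not the same as recruiting there, and the Discussion names a move to nationwide recruitment as a possible adaptation.
- **That green randomisation at 10 per month fails because 10 × 17 = 170.** The target of about 180 is stated as a number to recruit, and the randomisation limit is not derived from it.
- **That pairing the two lights implies conversion cut-offs (10/11, 4/5).** The plan states no such proportions.

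**Conclusion.** The point holds as a badly fixed criterion: a required average is judged by a maximum. At true rates of 8 to 9 per month, which need 20 to 22.5 months for 180, green has a probability of 46% to 65% over 3 months and 64% to 88% over 5 to 6 months. The chance of reaching 180 within 17 months is about 2% or less.

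These figures rest on constant-rate, independent Poisson counts and on assumed recruitment lengths. Overdispersion makes green at these rates more likely. The example of 11, 5, 5, 5, 5 needs no model.

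Two stronger readings are not supported. Rates below 10.6 do not make 180 unattainable; they make it unattainable on average within the designated 17 months. Nor do the documents show that this trial's light was green at too low a rate, because they give neither the number enrolled nor monthly counts.

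**What to change.** - **Recruitment.** Base the conclusion about the definitive trial on the mean monthly rate over the enrolment period, with an exact Poisson 95% CI, compared with 180/17 = 10.6 per month. Use 10.6 and not 11, since 10.7 × 17 = 182 already meets the target. Define the start and end of the period, because recruitment opened in November 2024 and the first enrolment followed in December.
- **Prespecified light.** Keep the best-month light and show it beside the mean rate. Disclose the mean-rate criterion as added after data collection.
- **Randomisation.** Report randomised over included participants as a proportion next to the existing light, without new cut-offs.

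The cost is a change of wording and reporting; the enrolment log already holds the data. The verdict may be less favourable. The interval will be wide (7.4 to 13.2 per month for 50 in 5 months), so it may not separate an adequate rate from an inadequate one, and the report should say so.

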### Statistical Analysis

#### Feasibility

All statistical analyses will be performed using Stata 17 (StataCorp LLC). To address the objectives of establishing the feasibility of this trial’s methodology and delivery of the CliMACT training, descriptive statistics will be used (mean, SD, n, %). Evaluation of meeting important feasibility criteria will be based on a traffic light system with 3 categories, with green indicating that full feasibility is established, yellow indicating that feasibility is established, but study procedures need to be modified, and red indicating that feasibility is not established. Feasibility of trial methodology (objective 1) will be based on recruitment, randomization, and retention, and evaluated according to a priori determined cutoffs shown in Table 1, with the primary objective of establishing the feasibility of recruitment for a future efficacy-effectiveness RCT (that informed our justification of the sample size, see above). Feasibility of delivering the CliMACT training (objective 2) will be based on participant satisfaction, participant adherence, and mental health professional fidelity to the training protocol, and will also be evaluated according to predetermined cutoffs (Table 1).

**Table 1 table1:** Traffic light criteria for the feasibility of trial methodology and the feasibility of delivering the CliMACT^a^ training.

			Green		Yellow		Red

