## Results

Cocreation of this study design started in November 2023. Adaptation of the EMI to meet the needs of young people with climate change–related distress took place between February and September 2024. The trial was registered at ISRCTN (no. ISRCTN33613914) in November 2024. All study procedures were approved by the local ethics committee in September 2024 (Amendment I: November 2024). Recruitment started in November 2024, and the first enrollment was in December 2024. Data collection was completed by August 25, 2025. The results from the feasibility RCT are expected to be published in 2026. Its findings are going to inform the methodology of a fully powered efficacy-effectiveness RCT.

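### The recruitment limit of 11 per month is a 17-month average but is judged on the best pilot month, so the primary feasibility light leans towards green

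*Protocol article*

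**What the plan says.** In the protocol article, Measures (Feasibility of Trial Methodology) sets the recruitment criterion as "achieving the minimum monthly recruitment rate of 11 in (at least) the month with the highest recruitment rate". Justification of Sample Size (Feasibility RCT) explains the figure: "This lower bound reflects the minimum monthly recruitment rate required to recruit an expected ≈180 participants", within 17 months. It repeats the best-month wording and gives an upper rate of 17, which is 50 participants in 3 months.

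Table 1 applies the same statistic to each light:
- Green: "Monthly recruitment rate of n=11 to n=17 participants in (at least) the month with the highest recruitment rate".
- Yellow: "Monthly recruitment rate of n=5 to n=10 participants in (at least) the month with the highest recruitment rate", with the instruction to widen the recruitment area beyond Mannheim and Rhine-Neckar.
- Red: "A monthly recruitment of n<5 participants for all months of the feasibility RCT recruitment period".

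Randomization is also judged on its best month, with a green limit of 10. Statistical Analysis (Feasibility) defines "green indicating that full feasibility is established" and evaluates trial methodology "with the primary objective of establishing the feasibility of recruitment for a future efficacy-effectiveness RCT". No recruitment criterion uses the mean rate or the total time taken to recruit.

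**The concern.** The limit and the statistic compared with it are different quantities. Eleven per month is what must be achieved on average across 17 months. The best of several months is never below their mean and is usually above it, so a pilot can pass although its underlying rate is too low for the target.

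This bears on the objective the article names as primary and on which it bases the sample size. Only the yellow light carries the instruction to open the recruitment area, so a green light reached through one good month would remove the plan's own prompt for that remedy.

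**Working it through.** **1. The plan's own figures.** 180/17 = 10.59, rounded up to 11. 50/3 = 16.67, rounded up to 17. Both reproduce, and both are averages.

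**2. Assumptions.** Monthly counts are independent Poisson with a constant true mean λ. The article gives neither the month-to-month variation nor a fixed pilot window, so several windows are shown: 3 months (the one window the article names), 5 and 6 months (roughly compatible with first enrollment in December 2024, about 3.5 months per participant and data collection complete by August 25, 2025), and recruitment continuing until 50 are enrolled.

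**3. Chance of green under the best-month rule.** For a fixed window of m months, P(green) = 1 − P(X ≤ 10)^m. At λ = 8, P(X ≥ 11) = 0.184, so over 6 months P(green) = 1 − 0.816^6 = 0.705. The expected best of those 6 months is 11.7. The recruit-to-50 column is a simulation of 200,000 runs.

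| True mean | P(one month ≥ 11) | 3 months | 5 months | 6 months | Until 50 |
|---|---|---|---|---|---|
| 7 | 9.9% | 26.7% | 40.5% | 46.3% | 50% |
| 8 | 18.4% | 45.7% | 63.8% | 70.5% | 71% |
| 9 | 29.4% | 64.8% | 82.5% | 87.6% | 86% |

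With extra month-to-month variation (gamma-Poisson, shape 10, recruiting to 50) the figures are 69%, 83% and 91%.

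**4. What these rates deliver.** Expected total in 17 months = 17λ; months needed = 180/λ.
- 7 per month: 119 participants, 25.7 months to reach 180.
- 8 per month: 136 participants, 22.5 months.
- 9 per month: 153 participants, 20.0 months.

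The Poisson chance of at least 180 in 17 months is below 0.1%, below 0.1% and 1.8% respectively.

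**5. The same rates judged on the mean.** The window total must reach 10.59m, that is 53 in 5 months or 64 in 6. This treats the window as fixed and ignores the cap of 50. P(green) is at most 0.3% at a true 7, 2 to 3% at 8 and 10 to 13% at 9. At a true 10.59, just sufficient, it is 49 to 52%.

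**6. The red category.** At a true 3 per month, P(X ≥ 5) = 0.185. Yellow or better is reached with probability 1 − 0.815^m, which is 46%, 64% and 71% over 3, 5 and 6 months. Red therefore still occurs in 54%, 36% and 29%.

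**7. Precision of a pilot mean.** As an illustration only, suppose 50 participants in 6 months. The exact Poisson 95% CI for a count of 50 is 37.1 to 65.9. The rate is then 8.3 per month (6.2 to 11.0), and the 17-month projection is 142 (105 to 187).

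**The case against.** The best-month rule is stated openly and consistently in all three places, so it is a lenient prespecified choice and not a contradiction. It could be defended as measuring capacity once start-up is over. The article does not give that reason, however, and one peak month does not show that a rate lasts for 17. Nor does green launch the definitive trial automatically: the Discussion says the findings will guide recruitment sites and strategies and will be discussed with the society advisory group. That limits the consequence but leaves the mismatch in place.

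Four stronger readings are tempting, and the document does not support them:
- That 7 to 9 per month, sustained, is usually green. At 7 it is about even at best under Poisson variation, and over 3 months only 9 passes more often than not. Counts of 7 to 9 in every month would be yellow, so the statement concerns the true mean only.
- That red can practically never occur. Step 6 shows otherwise for pilot windows of 3 to 6 months. Near-certain escape from red at 3 per month would need recruitment to go on to 50, about 17 months (50/3 = 16.7).
- That this trial itself averaged below 10.6. The article gives no enrollment total, no day of first entry and no date of last entry. If 50 were enrolled with a last entry around May 11, 2025, a first entry on December 15 gives about 10.4 per month and one on December 31 about 11.6. The answer crosses the limit within the stated month.
- That the criterion can simply be replaced. The cutoffs are described as determined a priori and data collection is complete, so a silent substitution would be a post hoc change.

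**Conclusion.** The point holds for the mismatch and its direction. A limit derived as an average of 10.6 per month is applied to a maximum, so the light for the primary objective is biased towards green. A true mean of 8 to 9 per month is usually called green over 5 to 6 months or when recruiting to 50. At a true 7, green occurs about half the time when recruiting to 50, about 40 to 46% over 5 to 6 months and 27% over 3 months. These rates fall 27 to 61 participants short of about 180 in 17 months. The red category is weakened only. The percentages rest on assumed Poisson variation and assumed windows; the direction of the bias does not. The same best-month rule affects randomization, but the size was computed for recruitment only, because 11 is the limit whose derivation the article gives.

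**What to change.** - Report the prespecified best-month light for recruitment and randomization as planned.
- Base the conclusion on recruitment feasibility on the mean monthly rate over the recruitment period, compared with 180/17 = 10.6. Give its exact Poisson 95% CI and the projected 17-month total beside it. Treat randomization likewise, on its mean monthly rate.
- Label this as a change to the a priori criterion, made after data collection ended.
- State where the counting window starts. The article says "Recruitment started in November 2024, and the first enrollment was in December 2024", so the opening of recruitment and the first enrollment give different rates; show both.

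The cost is one division on data already held, plus wording in Measures, Justification of Sample Size and Table 1. There are two downsides. The result may be less favourable than the best-month light. A point-estimate rule on the mean is also green only about half the time at a rate that is just sufficient, and the interval will be wide. That is why the interval must be shown and the mean should not be read as a bare pass or fail.
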